### Subject population and inclusion/exclusion criteria

Systemically healthy volunteers with untreated generalized severe periodontitis (periodontitis stages III or IV, generalized [50];) are being selected from the Center for Clinical Trials of UNG and Periodontal Clinic of UFPR. Subjects are being selected according to the following inclusion criteria: presence of at least 15 teeth (excluding third molars and teeth indicated for extraction), at least 30% of the teeth with PD and CAL ≥ 4 mm, and a minimum of 6 teeth with at least one interproximal site each with PD and clinical attachment level (CAL) ≥ 5 mm. Exclusion criteria are as follows: pregnancy, breastfeeding, current smokers and former smokers—for at least 5 years [51], systemic diseases that could affect the progression of periodontitis (e.g., diabetes, immunological disorders, osteoporosis), SRP in the previous 12 months, antibiotic therapy in the previous 6 months, long-term intake of anti-inflammatory drugs, need for antibiotic pre-medication for dental treatment, use of orthodontic appliances, extensive prosthetic rehabilitation, and allergy to MTZ and/or AMX.

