### Clinical examination (baseline, 3, 6, and 12 months)

Two calibrated examiners, one from each center (UNG and UFPR), are performing the clinical evaluations and collection of biofilm, GCF, and blood samples. The following periodontal parameters are being evaluated: visible plaque [52], gingival bleeding (0/1), BOP (0/1), SUP (0/1), PD (mm), and CAL (mm) at six sites per tooth (mesiobuccal, buccal, distobuccal, distolingual/palatal, lingual/palatal and mesiolingual/palatal) in all teeth, excluding third molars. PD and CAL measurements are rounded to the nearest millimeter using a North Carolina periodontal probe (Hu-Friedy, Chicago, IL, USA).

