### Primary and secondary outcome variables

The primary outcome variable is the difference among groups for the percentage of volunteers achieving the clinical endpoint for therapy (≤ 4 sites with PD ≥ 5 mm) at 1 year post-treatment [57].

Secondary outcome variables are as follows: difference between baseline and 12 months post-therapy for mean CAL gain and PD reduction (in the full mouth and in different PD categories), mean number and percentage of volunteers with 0, 1–2, or ≥ 3 sites with different thresholds of residual pockets (e.g., PD ≥ 6 and ≥ 7 mm) at 12 months post-therapy; mean number (and mean reductions) of different thresholds of residual pockets at all post-treatment time points; difference among groups for the percentage of volunteers achieving different thresholds of BOP (e.g., ≤ 10%, 20% and 30% of bleeding sites in the mouth) at 1 year post-treatment; differences in the occurrence of adverse events among therapeutic groups; and differences in the counts and proportions of 40 bacterial species in the biofilm samples at all post-treatment time points and in the levels of 17 chemokines in the GCF and peripheral blood samples at 1 year post-therapy.

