### Randomization

The study coordinator ([name]), who is not involved in the inclusion and treatment of patients, assigned the study participants to one of the four treatment groups by means of a computer-generated random sequence (Random Allocation Software, http://random-allocation-software.soft). Randomization was stratified by center using permuted blocks of 4, 8, and 12. The study coordinator also organizes the bottles with the antibiotics tablets in opaque plastic bags labeled with the volunteer’s number. In addition, one clinical investigator and the study coordinator sent the randomization list to the *BioGaia AB Company* (Stockholm, Sweden). The company made and packed the probiotic (and placebo) lozenges in boxes labeled with each volunteer’s number. The bags are handed directly to the volunteer by the study coordinator. This sequence of procedures assures allocation concealment.

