### Statistical analysis

#### Clinical monitoring

The chi-square test will be used to compare the differences in the frequency of gender and to compare the differences in the frequency of subjects achieving the clinical endpoint for treatment (≤ 4 sites with PD ≥ 5 mm) at 1-year (primary outcome variable) and of self-perceived adverse effects. Each individual continue/categorical variable will be computed per subject and then across subjects in each group. The significance of clinical differences over the course of the study will be sought using repeated measures ANOVA or Friedman multiple comparison tests (and their respective post-hoc tests, when necessary), and at each time point (among groups), using either ANOVA or Kruskal-Wallis multiple comparison tests (and their respective post-hoc tests when necessary) or ANCOVA with adjustments for the baseline values. Parametric or non-parametric tests will be chosen based on the normality of the data. A stepwise forward logistic regression analysis will be performed to investigate the impact of predictor variables on the clinical endpoint for treatment, i.e., “presence of ≤ 4 sites with PD ≥ 5 mm at 1-year post-therapy (yes/no).” The Number Needed to Treat (NNT) with each treatment protocol in order to obtain treatment success (≤ 4 sites with PD ≥ 5 mm) will be calculated using the following formula: NNT = 1/ARR, where ARR = |CER − EER| and CER = control group event rate and EER = experimental group event rate (http://ktclearinghouse.ca/cebm/glossary/nnt). The level of significance will be set at 5%. The data will be evaluated using intention-to-treat analysis with last observation carried forward.

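### The primary chi-square uses neither centre nor the baseline number of deep sites: a valid test that leaves some precision unused

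*Protocol article*

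**What the plan says.** Under Primary and secondary outcome variables: "The primary outcome variable is the difference among groups for the percentage of volunteers achieving the clinical endpoint for therapy", defined as at most 4 sites with PD ≥ 5 mm at 1 year. Under Statistical analysis, Clinical monitoring, a chi-square is named "to compare the differences in the frequency of subjects achieving the clinical endpoint for treatment", and no stratum or covariate is attached to it. The abstract says the same.

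Other places bear on this:

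- Randomization: "Randomization was stratified by center using permuted blocks of 4, 8, and 12".
- Clinical examination: each of the two centres has its own single examiner. PD is recorded at six sites per tooth at baseline and at every later visit.
- Subject population: entry requires "a minimum of 6 teeth with at least one interproximal site each with PD and clinical attachment level (CAL) ≥ 5 mm". This is a lower limit only.
- Clinical monitoring, on the same endpoint: "A stepwise forward logistic regression analysis will be performed to investigate the impact of predictor variables on the clinical endpoint for treatment". No term is said to be forced in.
- Clinical monitoring, for comparisons among groups at each time point: ANOVA or Kruskal-Wallis, "or ANCOVA with adjustments for the baseline values".

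**The concern.** Two variables known before treatment are left out of the primary test. Centre is the stratification factor, and with one examiner per centre it also carries any remaining difference in probing between examiners. The baseline number of sites with PD ≥ 5 mm is a likely predictor because the endpoint is an absolute count. Someone entering with 6 such sites must resolve 6 − 4 = 2 of them; someone entering with 60 must resolve 60 − 4 = 56. The spread can be wide: entry requires at least 6 such sites, while even the minimum of 15 teeth gives 15 × 6 = 90 probed sites.

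The article accepts baseline adjustment as an option for other comparisons but not for the primary one. The stepwise model cannot fill the gap. Forward selection may leave out treatment, centre or baseline extent, and p-values and intervals taken after selection do not have their nominal properties. At stake is the precision of the main comparison in a trial with about 37 evaluable participants per arm.

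**Working it through.** **1. The plan's own figure.** From Sample size calculation: a 30-point difference, 5% significance, 80% power, 37 per group, 15% attrition, 44 per group, 176 in total. The two rates and the sidedness are not given; two-sided is assumed. For an unadjusted comparison of two proportions,

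n = [1.96·√(2p̄(1−p̄)) + 0.842·√(p₁(1−p₁) + p₂(1−p₂))]² / (p₂−p₁)².

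- At 16% v 46%, p̄ = 0.31: (1.96·√0.4278 + 0.842·√0.3828)² / 0.09 = 36.1, so 37.
- The formula gives exactly 37 at a lower rate of 16–17% (mirror 53–54%).
- At 25% v 55%, p̄ = 0.40: (1.96·√0.48 + 0.842·√0.435)² / 0.09 = 40.7, so 41.
- Enrolment: 37 / 0.85 = 43.5, so 44; 44 × 4 = 176.

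The stated number is therefore that of an unadjusted two-proportion test, and it agrees with the planned chi-square.

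**2. What adjustment would add.** Simulation of two arms of 37 in two equal centres, 4,000 runs per setting. The model is logit P(success) = a(arm) + βₓx + β_c c, with x a standard normal baseline covariate, c = ±0.5 for centre, and a(arm) set so that the marginal rates are 16% v 46% or 25% v 55%. The odds ratios are assumptions: baseline 1, 1.65, 2.2 or 3.3 per SD; centre 1, 1.65 or 2.7. Ranges below run over the three centre values. Gain is the adjusted likelihood-ratio (LR) test minus the chi-square in the same setting.

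| Rates | Baseline OR per SD | Chi-square power, % | Centre + baseline, LR, % | Gain, points |
|---|---|---|---|---|
| 16 v 46 | 1 | 81.2–82.0 | 82.5–83.2 | 1.1–1.8 |
| 16 v 46 | 1.65 | 81.6–82.9 | 83.8–86.2 | 2.2–3.3 |
| 16 v 46 | 2.2 | 81.7–82.4 | 86.4–87.9 | 4.6–5.5 |
| 16 v 46 | 3.3 | 82.0–82.4 | 89.6–90.1 | 7.5–7.9 |
| 25 v 55 | 1 | 74.0–76.0 | 76.2–79.3 | 1.6–3.3 |
| 25 v 55 | 1.65 | 75.3–75.7 | 79.3–81.0 | 4.0–5.5 |
| 25 v 55 | 2.2 | 75.0–75.8 | 81.7–83.2 | 6.4–7.4 |
| 25 v 55 | 3.3 | 75.5–76.4 | 86.3–87.0 | 10.1–11.4 |

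**3. Centre alone.** A Cochran-Mantel-Haenszel test by centre changes power by about 0 to 2 points. The logistic LR test with centre adds 1.2 to 3.8 points.

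**4. Validity.** With both arms at 31%, the chi-square rejected in 4.9–5.2% of runs and the LR test with centre and baseline in 5.7–6.3%. Even the unadjusted LR test had 0.7 to 1.4 points more power than the chi-square, so about 1 point of each gain is test liberality and not information.

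**5. Four arms.** With rates 25/40/55/55% and a 3-df test, the chi-square had about 73–75% power, and centre plus baseline 79–85% for baseline odds ratios of 1.65 to 3.3. The pattern is the same.

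**The case against.** The other side has a strong case, and most of it stands.

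- Nothing is invalid. The chi-square holds its level and the sample size was built for it. A reader might infer that chance imbalance in baseline extent, or a difference between examiners, biases the result. It does not: a randomised test already allows for chance imbalance, and blocks within centre balance the examiner across arms. Investigator' calibration also says that both examiners were calibrated before the trial, with yearly repetition.
- The gain rests on prognostic strengths and rates that the article does not state. If neither factor is prognostic, nothing is gained beyond liberality.
- The simulations use 37 per arm. The article plans intention-to-treat with last observation carried forward, so up to 44 per arm may be analysed. The unadjusted power at 44 is then about 88% at 15% v 45% and 83% at 25% v 55%, which leaves less to gain.
- A reader might infer that the stepwise model decides the treatment question. Its stated purpose is to explore predictors, so its selection cannot alter the primary test. Its candidate list may sit in an analysis plan that is not shown, and its absence here is not counted against the article.
- A reader might also infer that the plan has no baseline adjustment at all. It offers ANCOVA for other comparisons; the gap concerns the binary primary endpoint only.

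What survives is narrower. The article does commit to a specific primary test, that test omits the stratification factor and a recorded, plausible predictor, and no pre-specified adjusted treatment effect on the primary endpoint is named.

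**Conclusion.** The point holds as a recommended improvement, not as an error. The planned test is valid and consistent with 37 per group; it is less precise than the recorded data probably allow. At 37 per arm the total gain from centre plus baseline extent is about 2 to 5.5 points of power for a weak baseline predictor (odds ratio 1.65 per SD), 4.5 to 7.5 for a moderate one (2.2) and 7.5 to 11.5 for a strong one (3.3), each including about 1 point of LR liberality. Centre alone contributes about 0 to 4 points, so any material gain comes from baseline extent.

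These figures assume equal centres, a normally distributed baseline covariate, and event rates not in the article. They do not show that the trial is underpowered or that power is certainly lost. At 16% v 46% the unadjusted test already has its planned 80%. At 25% v 55% with 37 per arm it has about 75%, but that shortfall reflects the assumed rates and not the lack of adjustment.

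**What to change.** While the trial is still blinded, pre-specify as the primary analysis a logistic regression with treatment (four groups), centre and the baseline number of sites with PD ≥ 5 mm all forced in, and state the form in which the baseline count enters. Report standardised risk differences between groups with 95% CIs. These stay on the percentage-point scale of the sample size and can feed the planned number needed to treat. Keep the chi-square as a sensitivity analysis.

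Label the stepwise regression exploratory and do not report its treatment term as the adjusted treatment effect. A fixed predictor list that always contains treatment, centre and baseline extent would be better still.

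The cost is a change of analysis wording; every variable is already collected and no participants are added. The small downside is the slight liberality of the LR test at this sample size, which a score test or a robust standard error for the standardised risk difference can limit.

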**Methods:**

Subjects with periodontitis are being randomly assigned to receive (i) SRP alone, or with (ii) two probiotic lozenges/day for 90 days (Prob), (iii) MTZ (400 mg) and AMX (500 mg) thrice a day (TID) for 14 days (MTZ+AMX), or (iv) Prob and MTZ+AMX. Subjects are being monitored for up to 12 months post-treatment. Nine subgingival plaque samples per patient are being collected at baseline and at 3, 6, and 12 months post-therapy and analyzed by checkerboard DNA–DNA hybridization for 40 bacterial species. Peripheral blood and gingival crevicular fluid (GCF) of four randomly selected periodontal sites will be analyzed by means of a multiplex fluorescent bead-based immunoassay for 17 cyto/chemokines.

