### Interventions

At baseline, all volunteers fulfill a structured questionnaire to collect information about demographic, oral, and general health data. Subsequently, a complete periodontal clinical assessment and subgingival biofilm sampling are performed. One week later, gingival crevicular fluid (GCF) and peripheral blood samples are collected. Patients receive oral hygiene instruction (OHI), including tooth brushing and interproximal dental hygiene (using dental floss and interdental brushes). Other elements may be indicated according to individual needs, such as subjects with removable prostheses. In addition, supragingival scaling using ultrasonic scaler (Cavitron® Select™ Ultrasonic Scaler, Denstply, New York, USA) and curettes (Millenium, GOLGRAN, São Caetano do Sul, SP, Brazil) are performed. The plaque index is repeated 1 week after OHI and supragingival plaque removal. Subsequently, each volunteer is randomly allocated to one of the following therapeutic groups: (i) c*ontrol*: SRP +two antibiotic placebo pills three times a day (TID) for 14 days + two probiotic placebo lozenges a day for 90 days; (ii) *probiotic* (test 1): SRP + two antibiotic placebo pills TID for 14 days + two probiotic lozenges a day for 90 days; (iii) *antibiotic* (test 2): SRP + MTZ 400 mg and AMX 500 mg TID for 14 days + two probiotic placebo lozenges a day for 90 days; and (iv) *antibiotic + probiotic* (test 3): SRP + MTZ 400 mg and AMX 500 mg TID for 14 days + two probiotic lozenges a day for 90 days (Figs. 1 and 2).

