### Immunological monitoring (baseline and 12 months)

#### Serum and GCF sampling

Peripheral blood samples and GCF are being collected 1 week after clinical examination. Two non-contiguous diseased sites (i.e., PD and CAL > 5 mm, BoP and no furcation involvement) and two non-contiguous healthy sites (i.e., PD and CAL < 4 mm without BOP and/or gingival bleeding) are being randomly chosen per patient for GCF sampling (among the same sites selected for microbiological sampling). After removal of the supragingival biofilm, the selected sites are isolated with cotton rolls and gently dried with an air syringe to eliminate saliva. GCF is collected by inserting standard paper strips (Periopaper, Oraflow Inc., Smithtown, NY, USA) up to approximately 2 mm into the sulcus/pocket for 30 s. Strips visually contaminated with blood are discarded. The GCF volume is measured in a calibrated device (Periotron 8000, Proflow Inc., Amityville, NY, USA), and the readings are converted into an actual volume (microliter, μl) by reference to a standard curve. Strips from the four selected sites are immediately placed into separate microcentrifuge tubes and stored at − 80 °C for subsequent assays. Peripheral blood samples are into an appropriate tube (Serum BD Vacutainer Plus Plastic Serum Tubes, BD, Franklin Lakes, NJ). Fasted samples are obtained in the morning for all patients. Immediately after blood collection, the serum is separated from blood by centrifugation (10 min at 1300 rpm) and stored in aliquots at − 80 °C.

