### Sample size calculation

The ideal sample size to assure adequate power for this study was based on the percentage of volunteers achieving “≤ 4 sites with PD ≥ 5 mm” at 1 year post-treatment [57]. Considering a difference of 44 percentage points between groups for volunteers achieving this clinical endpoint at 1 year post-treatment [5] and a significance level of 5%, 17 subjects per group would be necessary to provide a power of 80%. Considering an attrition of 25%, it was established that at least 22 subjects should be included in each treatment group. Considering a difference of 30 percentage points between groups for volunteers achieving this clinical endpoint at 1-year post-treatment and a significance level of 5% 37 subjects per group would be necessary to provide a power of 80%. Considering an attrition rate of 15%, it was established that 44 volunteers should be included in each treatment group (total 176 subjects).

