#### Microbiological and immunological monitoring

Microbiological data will be expressed in counts (levels) and proportion counts of DNA probes. Mean counts will be expressed as counts × 10^5^. Microbial data will be calculated at each site for each volunteer and then across volunteers within each group, at each time point. The sum of the mean proportions of individual bacterial species will be computed for each microbial complex described by Socransky et al. [58]. The concentration and total amount of each cytokine/chemokine in the GCF will be assessed per volunteer and then per volunteer within each group at each study time point. Immunological data will be calculated at each site for each volunteer and then across volunteers within each group, at each time point. The significance of differences in microbiological and immunological parameters over the course of the study will be sought using repeated measures ANOVA or Friedman multiple comparison tests (and their respective post-hoc tests, when necessary) and at each time point (among groups) using either ANOVA or Kruskal-Wallis multiple comparison tests (and their respective post-hoc tests when necessary) or ANCOVA with adjustments for the baseline values. Parametric or non-parametric tests will be chosen based on the normality of the data.

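### If last observation carried forward is applied to the cytokine outcomes, which are sampled only at baseline and 12 months, anyone without a 12-month sample is scored with a pre-treatment level

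*Protocol article*

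**What the plan says.** The only missing-data rule in the protocol article closes the Clinical monitoring part of the Statistical analysis section: "The data will be evaluated using intention-to-treat analysis with last observation carried forward". It refers to the data in general, although its heading is clinical.

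The next part, Microbiological and immunological monitoring, lists its own tests: "The significance of differences in microbiological and immunological parameters over the course of the study will be sought using repeated measures ANOVA or Friedman" tests over time, and group comparisons at each time point by ANOVA, Kruskal-Wallis, "or ANCOVA with adjustments for the baseline values". It neither repeats nor replaces the missing-data rule.

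The sampling schedule is in the heading "Immunological monitoring (baseline and 12 months". The matching secondary outcome is the difference "in the levels of 17 chemokines in the GCF and peripheral blood samples at 1 year post-therapy". Under Interventions the baseline sample follows the first examination: "One week later, gingival crevicular fluid (GCF) and peripheral blood samples are collected". That section then describes hygiene instruction, supragingival scaling and random allocation, so the baseline sample comes before any study treatment.

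On attrition, the Sample size calculation says: "Considering an attrition rate of 15%, it was established that 44 volunteers should be included in each treatment group". No rate by arm is given.

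**The concern.** Clinical and microbiological measurements are also taken at 3 and 6 months, so for those outcomes a participant who leaves late has a post-treatment value to carry forward. The cytokine outcomes have no intermediate visit. Whenever a participant leaves before month 12, the only value available is the untreated baseline, and carrying it forward records no change over the year.

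Three consequences follow if the rule is applied here. The contrast between arms is diluted. The 12-month variance grows, because untreated and treated levels are mixed. And where arms lose different numbers of participants, a difference can appear that treatment did not cause. The last arises because all arms are actively treated ("Subjects with periodontitis are being randomly assigned to receive (i) SRP alone, or with" adjuncts), so the control mean is expected to move from baseline as well. Immunological effect is one of the three effects named in the study's aim, so these comparisons will be read as findings.

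**Working it through.** **The plan's own figure.** 37 / (1 − 0.15) = 43.5, rounded up to 44 per group, and 4 × 44 = 176, as stated. This figure serves the primary binary endpoint. The article gives no effect size, SD or power for cytokines.

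**Inputs from the document.** 44 per arm; 15% attrition, so 0.15 × 44 = 6.6 per arm and 4 × 6.6 = 26.4 in total without a 12-month sample; 44 × 0.85 = 37.4 per arm with one; 5% significance level; cytokines at baseline and 12 months only; scaling and root planing in every arm.

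**Assumptions not in the document.** Two-sided testing; normal data with SD 1 on the analysis scale; correlation 0.5 between baseline and 12 months; drop-out unrelated to level; a true difference of 0.57 SD, chosen because ANCOVA on observed values then has about 80% power; a fall from baseline common to the arms of 0 to 1.5 SD.

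**Expected difference.** Let c and t be the true mean falls in the control and treated arms, and dC and dT the drop-out rates. A drop-out contributes zero change, so the expected difference is (1 − dT)·t − (1 − dC)·c.

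- Equal drop-out d: this becomes (1 − d)(t − c). At 15%, 0.85 × 0.57 = 0.48 SD. Simulated estimates were 0.483 to 0.490.
- Unequal drop-out, true difference 0.50 (c = 1.0, t = 1.5):
  - control 20%, treated 10%: 0.90 × 1.5 − 0.80 × 1.0 = 0.55
  - control 10%, treated 20%: 0.80 × 1.5 − 0.90 × 1.0 = 0.30
  - control 25%, treated 5%: 0.95 × 1.5 − 0.75 × 1.0 = 0.675
  - control 5%, treated 25%: 0.75 × 1.5 − 0.95 × 1.0 = 0.175
- No true difference (t = c = m): the result is (dC − dT)·m. With rates 10 points apart, the false difference is 0.05, 0.10 or 0.15 SD for m = 0.5, 1.0 or 1.5.

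**Variance.** In an arm that falls by m, the 12-month variance under the rule is 1 + d(1 − d)m². At d = 0.15 and m = 1.5 this is 1 + 0.1275 × 2.25 = 1.29.

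**Power and type I error.** Simulated two-arm ANCOVA, 44 per arm (4,000 runs for the first two rows, 6,000 for the rest). Power is at 15% drop-out in both arms; type I error is at 10% versus 20%.

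| Common fall (SD) | Power, carried forward | Power, observed values | Type I error, carried forward |
|---|---|---|---|
| 0 | 76% | 79% | 4.3% |
| 0.25 | 75% | 80% | 5.3% |
| 0.5 | 73% | 80% | 5.8% |
| 1.0 | 67% | 80% | 8.1% |
| 1.5 | 57% | 80% | 10.5% |

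Repeat runs of the last three rows gave power of 73-74%, 65-66% and 56-58%, and type I error of about 6%, 8-9% and 11-12%. Observed-value ANCOVA held about 5% at falls of 0.5 to 1.5 SD. With equal drop-out the carried-forward analysis also stays near 5%.

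**The case against.** **Scope.** The rule stands under Clinical monitoring, and the immunological part sets out its tests afresh without it. The 5% level, stated beside the rule, is repeated in the abstract for the whole trial; the rule is not. A reader might infer that the plan definitely scores every drop-out's baseline as the 1-year cytokine result. The text does not go that far. What stands against a purely clinical reading is the unrestricted wording and the absence of any competing rule, so the point holds conditionally.

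**No rule at all.** A reader might also argue that, if the rule is clinical only, these participants have no rule. That is not a finding: an article may leave a missing-data rule for secondary biomarkers to the full protocol or analysis plan.

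**Direction.** It is tempting to say that the rule always shrinks the effect and costs only power. That is assured only with equal drop-out, and the article gives no rates by arm.

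**Size.** The larger losses need a common fall of 1.0 to 1.5 SD, for which the document gives no support. Two of the four GCF sites per patient are healthy at baseline, and serum is measured too; falls may be small there. At 0 to 0.25 SD the loss is a few points and type I error stays near 5%. The simulation also compares two arms under normality, whereas the plan compares four and allows rank tests. This objection stands: the sizes are a range, not a forecast.

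**Benchmark.** Observed-value ANCOVA looks clean because drop-out was assumed unrelated to level. The Interventions section removes participants with progressive attachment loss, so missingness may be related to outcome and completers may be biased too. This also stands, and is why the fix needs a sensitivity analysis.

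**Conclusion.** The point holds in conditional form. The document states a general carry-forward rule and a two-visit schedule for cytokines; put together, they enter a pre-treatment level as a 1-year outcome. With equal 15% attrition the attenuation is 15% by arithmetic, whatever the effect size. With unequal attrition, bias in either direction and a false difference are possible whenever the arms share a change from baseline.

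The power range (76% down to 57%, against about 80%) and the type I error range (about 5% up to 11-12% at 10% versus 20% drop-out) rest on the assumed correlation, effect, common fall and random drop-out. The upper ends should not be quoted alone. The outcomes are secondary, the trial was not sized for them, and the primary endpoint is not affected. The matter is worth correcting but does not threaten the trial's main conclusion.

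**What to change.** In the Microbiological and immunological monitoring part of the analysis section:

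- State that last observation carried forward does not apply to GCF and serum outcomes.
- Analyse the observed 12-month samples with the baseline-adjusted ANCOVA already listed there.
- As a sensitivity analysis, use multiple imputation from treatment, centre, baseline level and the 3- and 6-month clinical data, because drop-out, including withdrawal for attachment loss, may be related to outcome.
- Report the number sampled at 12 months in each arm.

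This takes a few sentences and no new data, visits or participants. The cost is that the analysed number for these outcomes falls from 44 to about 37 per arm at the planned attrition, which is the number actually measured.
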